Barriers and enablers to responsive feeding for caregivers were identified in a systematic review of responsive feeding behaviours [18]. Barriers and enablers within five COM-B domains were identified: psychological capacity, physical and social opportunity, reflective and automatic motivation. For example, barriers to responsive feeding including not recognising developmental signs and feeding cues, having feeding goals, feeling stigmatised by HCP attitudes for formula feeding and also written instructions on formula opposing responsive feeding practices can discourage responsive feeding. Enablers such as caregivers being able to recognise infant feeding cues and being given advice and support from HCPs, family and peers were identified as facilitating responsive feeding. This systematic review identified the behaviours to target within an intervention to improve responsive infant feeding. It also highlighted the need for responsive feeding interventions for caregivers to be developed in tandem with guidance for HCPs. Such HCPs include midwives, health visitors and support workers such as family mentors who work with families to provide advice and support including around infant feeding.

Having established the evidence base for responsive feeding intervention development, the MRC Framework [23] further emphasises engaging and working with stakeholders at each stage of designing and conducting intervention research to maximise the likelihood that interventions are fit for purpose and have positive impacts on health outcomes. Therefore, the co-creation of interventions with caregivers and HCPs such as health visitors, infant feeding leads and support workers who work with caregivers and offer infant feeding advice and support is vital to support responsive feeding. The framework also highlights considering the implementation of the intervention during its development to increase the likelihood that the intervention can be effectively transferred into real-world settings.

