## 2. Materials and Methods

### 2.1. Design

This is a mixed-method study involving qualitative co-design workshops with caregivers and HCPs/support workers and a combination of quantitative and qualitative approaches to inform RLO development and evaluation. A mixed-method design enables us to gather comprehensive information from both caregivers and HCPs beyond that which would be possible from a single quantitative or qualitative approach. In addition, the use of qualitative, interactive approaches enables more in-depth and rich data which are complemented by the broader reach of data captured via the survey approaches used. This study does not involve quantitative hypothesis testing and instead involves an exploratory survey approach where sample size calculations have not been conducted. This study will instead aim to recruit a broad representative sample of participants to address the research aim.

The BCW framework [21] and the Behaviour Change Techniques Taxonomy (BCTT) [28] will be utilised to co-create a behaviour change RLO with caregivers, HCPs and support workers. The Am, **S**toryboarding, **P**opulate specification, **I**mplement media, **R**eview and release prototype, **E**valuate (ASPIRE) approach [29] for designing digital education resources will be used, including stakeholder involvement in co-designing the RLO and infographic for HCPs and support workers. As part of the final evaluation step, preliminary summative and formative evaluation of the usability, acceptability and implementation of the RLO and infographic will be undertaken.

Due to the lack of guidelines for the reporting of mixed-method research, the Consolidated Criteria for Reporting Qualitative Research (COREQ) checklist [30] will be followed in conducting and reporting this research.

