##### Method and Analysis

*Workshop 3.* We will decide on the most appropriate and feasible intervention components including BCTs and content. The potential content and BCTs developed in phase 2 will be presented to the caregivers and HCPS/support workers by the workshop facilitators. The identified intervention functions will be checked against each of the six APEASE criteria [21]: affordability, practicability, effectiveness and cost-effectiveness, acceptability, side effects/safety and equity. The whole group will consider each individual intervention function against each of the six APEASE criteria to help identify the most appropriate intervention functions to use in the RLO.

The facilitators will present all BCTs that could be considered for each intervention function, identified within phase 2. The number of BCTs will be reduced by using each of the APEASE criteria to find the most appropriate and feasible BCTs to use in the RLO. We will reach a consensus on which BCTs to include in the RLO by ranking each of the ideas by preference to use within the RLO.

The output of the workshop will be a consensus of what should be included in the final RLO and how this should be delivered.

*Workshop 4.* The participants will include caregivers, HCPs and technologists from the University of Nottingham’s health e-learning and media team (HELM) and will use the ranked topic ideas and BCTs from workshop 3 to work on how these can be represented pedagogically and visually in the RLO. The workshop will explore with the participants any analogies, anecdotes, images, videos and personal stories that will engage learners and facilitate their understanding of the ideas and guidance. A0 laminated storyboard templates will be provided for participants to express their ideas in text or drawings. Facilitators will direct the participants using a crib sheet outlining the Theoretical Domains Framework (TDF) with COM-B in order to identify the essential components or ‘active ingredients’, i.e., the visual and graphic elements that represent the knowledge, skills and motivational aspects incorporated into the RLO to bring about the desired behaviour change (responsive feeding)—for example, some of the components that the RLO might address are shown in Table 1.

The output of this workshop will be the creation of a storyboard of caregiver responsive feeding behaviours. In addition, this workshop will concentrate on how to translate non-caregiver behaviours into practice.

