##### Recruitment for Evaluation

We will conduct a preliminary evaluation of the functionality, acceptability and usability of the RLO. Caregivers, HCPs and support workers (who were not part of the RLO development) will be recruited for either a formative survey or one of two summative surveys. Potential participants will be emailed a link to the RLO, patient information sheet (PIS), informed consent form (ICF) and respective survey. Participants will be given up to two weeks to access and complete the surveys and will be able to work through the RLO as many times as they require during this two-week period.

Survey 1—Up to 20 caregivers, HCPs and support workers will be asked to review the prototype RLO for content and ease of use.

Survey 2—Up to 30 caregivers will be recruited via Small Steps Big Changes (https://www.smallstepsbigchanges.org.uk/) and public contributors.

Survey 3—Up to 30 HCPs and support workers will be recruited via contacts at the Institute of Health Visiting and the Royal College of Midwives and gatekeepers at local NHS trusts who will be asked to send the survey via email to HCPs and support workers.

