*Survey 1* (formative) responses will explore the usability of the RLO content and functionality and will be completed by caregivers, HCPs and support workers. The questions have been adapted from a survey tool by Johnson et al. exploring the usability of an e-learning resource to improve the knowledge and confidence of teachers working with children born pre-term [35]. Survey 1 (see Appendix A Table A1 survey A1) will consist of 9 closed questions with responses of agree, neutral or disagree to questions such as “the CRIB-RLO resource held my interest”.*Survey 2* (summative) (see Appendix A Table A2 survey A2) will be completed by caregivers and will ascertain the impact of the RLO on caregivers in terms of changing behaviours related to responsive feeding. There will be 7 closed questions on a 3-point scale from agree, neutral and disagree, including questions such as “The CRIB-RLO resource has improved my confidence in knowing how to feed my baby” and “The CRIB-RLO resource has increased my motivation to actively look for and respond to my babies cues during feeding”.*Survey 3* (summative) (see Appendix A Table A3 survey A3) will be completed by HCPs working with caregivers of infants and will explore the implementation of the RLO and infographic in practice within the NHS and other organisations. The questions have been developed based on a the Theoretical Framework of Acceptability (TFA) developed by Sekhon et al. [36]. The TFA can be used to evaluate the prospective and retrospective acceptability of healthcare interventions by both intervention deliverers and intervention participants. Preliminary reliability testing on the Sekhon et al. TFA adapted for examining the implementation of a telephone-assisted coaching framework revealed three main factors. These are affective attitude and effectiveness (Cronbach’s alpha 0.9, coherence and understanding (0.77), perceived burden (0.85), and suggesting an appropriate level of internal consistency for each construct [37].

Survey 3 will include a mixture of eight open and two closed questions on the implementation of the RLO in practice. Open questions include those such as “Can you describe any additional effort you might need to employ to implement the CRIB-RLO/Infographic into practice?” and closed questions such as “how prepared are you to deliver the CRIB RLO to caregivers?” with a 5-point Likert scale ranging from not at all prepared to highly prepared.

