## Appendix A

**Table A1 healthcare-12-00029-t0A1:** Survey A1: Usability of the CRIB-RLO.

Part 1 The CRIB-RLO resource ^1^ *Please indicate the extent to which you Agree, are Neutral or Disagree, with the following statements*		
The CRIB-RLO resource held my interest.		
Agree	Neutral	Disagree
2. I enjoyed using the CRIB-RLO resource.		
Agree	Neutral	Disagree
3. I found the CRIB-RLO resource easy to use.		
Agree	Neutral	Disagree
4. The visual elements added to my understanding of the topic.		
Agree	Neutral	Disagree
5. The audio commentaries were engaging.		
Agree	Neutral	Disagree
6. The case studies were engaging.		
Agree	Neutral	Disagree
7. I would prefer to use the CRIB-RLO resource than read written information.		
Agree	Neutral	Disagree
8. It was clear from the learning objectives what was in each section.		
Agree	Neutral	Disagree
9. I would recommend the CRIB-RLO resource to other caregivers or healthcare professionals/support workers.		
Agree	Neutral	Disagree
10. If you Disagree with any of the above statements, please add your suggestions for improving this resource?		
Final Version 1.1, 04/07/2023, IRAS 326807, FMHS 238 0323		

^1^ Questions derived from a survey tool used by: Johnson, S.; Bamber, D.; Bountziouka, V.; Clayton, S.; Cragg, L.; Gilmore, C.; Griffiths, R.; Marlow, N.; Simms, V.; Wharrad, H.J. Improving developmental and educational support for children born preterm: Evaluation of an e-learning resource for education professionals. *BMJ Open*
**2019**, *9*, e029720. https://doi.org/10.1136/bmjopen-2019-029720 [35].

**Table A2 healthcare-12-00029-t0A2:** Survey A2: Impact on caregivers.

Part 1 You			
Please indicate if you are a caregiver or a member of the CRIB public contributors group?			
*Please tick the box*			
Caregiver			
Public contributor			
If you are a caregiver, do you have a child less than one year old?			
Yes			
No			
2. Were you involved in the development of the CRIB-RLO resource?			
Yes			
No			
3. If you would like a link to the final resource please provide your email address below			
Part 2 Your learning			
*Please indicate the extent to which you Agree, are Neutral or Disagree, with the following statements*			
The CRIB-RLO resource has improved my understanding of when my baby is hungry and when they are full.			
Agree	Neutral	Disagree	
2. I am more likely to feed my baby based on their cues or signs than other ways for example, other people’s advice.			
Agree	Neutral	Disagree	

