3. I am more likely to feed my baby based on their cues or signs than other ways such as instructions on baby food tins.			
Agree	Neutral	Disagree	
4. The CRIB-RLO resource has improved my confidence in knowing **how** to feed my baby.			
Agree	Neutral	Disagree	
5. The CRIB-RLO resource has improved my confidence in knowing **when** to feed my baby.			
Agree	Neutral	Disagree	
6. The CRIB-RLO resource has helped me understand when it might be more difficult to read my babies signs and cues.			
Agree	Neutral	Disagree	
7. The CRIB e-learning resource has increased my motivation to actively look for and respond to my babies cues during feeding.			
Agree	Neutral	Disagree	

**Table A3 healthcare-12-00029-t0A3:** Survey A3: HCPs implementation into NHS/other organisations.

Part 1 You					
1. Please indicate your main area of work?					
					*Please tick the box*
Health visitor					
Parent support worker					
Midwife					
Children’s Nurse					
Nursery Nurse					
Breastfeeding or lactation consultant					
Other, please state					
2. Please indicate your employing organisation?					
Nottinghamshire Healthcare NHS					
Nottingham City Care Social Enterprise					
United Hospitals Lincoln					
Local Authority					
Charity or NGO					
Higher Education					
Other, please state					
3. Were you involved in the development of the CRIB-RLO resource?					
Yes					
No					
4. If you would like a link to the final resource please provide your email address below					
Part 2 Please provide your views on the CRIB-RLO and the Infographic ^1^					
Please indicate how you feel about the CRIB-RLO and Infographic?					
2. Can you describe any additional effort **you** might need to employ to implement the CRIB-RLO/Infographic into practice?					
3. Is the CRIB-RLO/Infographic a good fit with your own values around how you give infant feeding advice? Please describe any areas where there is conflict.					
4. Do you understand the information contained in the CRIB-RLO/Infographic?					
5. Do you think the CRIB-RLO/Infographic work well together as a way of improving caregiver responsive feeding?					
6. What aspects of the process of providing infant feeding advice in your team/organisation might alter as a result of caregivers having access to the CRIB-RLO?					
7. On a scale of 1-5 how effective do you think the CRIB intervention will be in changing the way caregivers feed their infants?					

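### Survey 2 cannot tell caregivers made worse from caregivers unchanged: Disagree on the change items covers both, and there is no comment field

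*Protocol article*

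**What the plan says.** Section 2.3.4 (Method) gives Survey 2 its purpose: it "will ascertain the impact of the RLO on caregivers in terms of changing behaviours related to responsive feeding". The format is fixed there too: "There will be 7 closed questions on a 3-point scale from agree, neutral and disagree". Table A2 Part 2 prints the instruction, "Please indicate the extent to which you Agree, are Neutral or Disagree, with the following statements", and the items:

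- Items 1, 4 and 5 credit the RLO with an improvement. Items 4 and 5 both begin "The CRIB-RLO resource has improved my confidence in knowing" and differ only in how versus when to feed.
- Item 7 credits it with increased motivation.
- Item 6 says that it helped the caregiver understand when cues are harder to read.
- Items 2 and 3 say that the caregiver is more likely to follow cues than other guides, without mentioning the RLO.

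The only write-in field in Table A2 is for an email address. The Analysis section plans frequency tables and descriptive statistics of the closed answers.

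By contrast, Survey 1 (Table A1, item 10) invites suggestions from anyone who disagrees, and Survey 3 gives professionals open questions.

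**The concern.** A survey meant to ascertain impact should be able to register an effect in either direction. Here the response scale measures agreement with a favourable statement, not direction of change. Rejecting a statement of improvement says only that there was no improvement. No later analysis can recover the direction, because it was never collected.

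At stake is how the result is read. A batch of Disagree answers on confidence in knowing when to feed could mean that the resource added nothing, or that it unsettled people. Those two readings would call for different revisions of the content, and Survey 2 offers no comment box in which a caregiver could say which applies.

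**Working it through.** The protocol gives no figure to reproduce. Section 2.1 states: "This study does not involve quantitative hypothesis testing and instead involves an exploratory survey approach where sample size calculations have not been conducted". The check is therefore a reading of the form plus a simple bound.

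**Inputs**
- Sample size: "Up to 30 caregivers will be recruited via Small Steps Big Changes" and public contributors (Recruitment for Evaluation). I take n = 30, which is a ceiling.
- Items and response options: Table A2 Part 2.
- Disagree counts and true rates of worsening: not in the protocol; the values below are assumptions for illustration.

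**What each answer on items 1, 4, 5 and 7 can mean**

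| Caregiver's experience | Answers available |
|---|---|
| Better | Agree |
| No change | Neutral or Disagree |
| Worse | Disagree (Neutral not excluded) |

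Neutral does not resolve the problem. An unchanged caregiver may tick either Neutral or Disagree, so Disagree cannot be read as worse.

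**Bound.** If d of n respondents tick Disagree, the number made worse among them lies between 0 and d, so their share of all respondents lies between 0 and d/n. At n = 30:

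| d | Possible share worse |
|---|---|
| 0 | 0 |
| 3 | 0 to 3/30 = 10% |
| 6 | 0 to 6/30 = 20% |
| 9 | 0 to 9/30 = 30% |

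The form cannot narrow these ranges. It is not wholly silent: if worsened caregivers tick Disagree, a low Disagree count limits how many there can be.

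**What a two-sided scale would add at n = 30**
- Chance of at least one worse answer, 1 − (1 − p)^30: for p = 2%, 1 − 0.98^30 = 45.5%; for p = 5%, 1 − 0.95^30 = 78.5%; for p = 10%, 1 − 0.90^30 = 95.8%.
- If nobody answered worse, the one-sided 95% upper limit would be 1 − 0.05^(1/30) = 9.5%.

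The first line is the chance that an affected person is among the respondents and reports it when asked. It is not a property of the present form.

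**Other routes in the protocol**
- Section 2.3.3: workshop 3 applies the APEASE criteria, "affordability, practicability, effectiveness and cost-effectiveness, acceptability, side effects/safety and equity", to intervention functions and BCTs. After workshop 4, advisory committee members review the detailed specification.
- Section 2.3.4 (Method): public contributors, including caregivers with different feeding choices, review content for accuracy and the prototype for fit of content and media.
- Survey 1: free text on improving the resource, from participants recruited to that survey instead of Survey 2.
- HELM's optional feedback after the project: usage and utility.

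As described, none of these asks caregivers what the resource did to them.

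**The case against.** The strongest reply is that this is a preliminary, exploratory evaluation. Objective 3 is initial acceptability, there is no hypothesis test, and effectiveness is left to a future randomised trial. A one-off anonymous survey of at most 30 users of a 15 to 20 minute resource need not be a harm instrument. Caregivers with differing feeding choices also see content and prototype beforehand, and Survey 1 respondents can comment. This stands as a limit on importance. It does not remove the point, because the protocol itself gives Survey 2 an impact purpose and the instrument is already printed.

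A two-sided scale after a single exposure would still have no baseline or comparator. That is true: the answers remain self-report, but they would at least carry a direction.

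Three stronger readings are tempting and are not supported:

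- *A risk named in the plan goes unmeasured.* The sections available name no specific risk of the RLO. Side effects and safety appear as one generic APEASE criterion, and "feeling stigmatised by HCP attitudes for formula feeding" (Introduction) is listed as an existing barrier to responsive feeding, not as an effect of the resource. Section 2.4 was not available to me, and I infer nothing from it.
- *Unwanted effects are considered only in workshop 3, before any content exists.* Workshop 3 already discusses potential content, and the later specification, content and prototype reviews could raise objections.
- *A harmful resource would pass through Survey 2 to release and a trial.* No section shown makes either step conditional on Survey 2.

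**Conclusion.** The point holds as a measurement limitation of a fixed instrument. On items 1, 4, 5 and 7, Disagree merges no change with worse, so Survey 2 can report benefit or its absence but cannot identify deterioration. The uncertainty is the whole Disagree count, from 0 to d. This rests on the printed wording and on the ordinary meaning of disagreeing with a statement of improvement, not on any assumed rate. The percentages do depend on assumed counts or rates and on all 30 places being filled.

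Items 2, 3 and 6 are also favourably worded, but they are not simple statements of improvement or increase and fall outside the main point. Given the exploratory aim and the partial routes elsewhere, this is a cheap improvement that lets the survey answer its own question.

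**What to change.** In Table A2 Part 2:

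1. Reword items 1, 4, 5 and 7 with neutral stems and a two-sided three-point scale. For item 5, for example: *Since using the CRIB-RLO, my confidence in knowing when to feed my baby is: worse / no change / better.* Item 7 could use lower / no change / higher.
2. Add one open comment field, as in Survey 1, and analyse it with the content analysis already planned for Survey 3's open answers.
3. In the Analysis section, state that the number of worse answers will be reported for each of the four items.

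If the form is to stay as it is, state in the protocol and the report that Survey 2 cannot assess worsening and that Disagree means only that no improvement was reported.

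The cost is a minor amendment to the survey version and one or two extra minutes per respondent on a form expected to take no more than 20.

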Caregivers seeking health information for their children have reported using the internet as their main source of information and reported high levels of confidence [25], and individuals seeking health information will most often use mobile devices [26]. However, a review of websites on infant health promotion including infant feeding found that the quality, accessibility and readability of the information was poor or adequate [27], highlighting the need for the development of interventions for caregivers and HCPs to be evidence-based, appropriate and useable.

The Public, Patient, Involvement and Engagement (PPIE) group who informed the development of this funding application suggested that any intervention around responsive feeding should utilise digital technology. Therefore, this research aims to develop an app to deliver a behaviour change intervention to caregivers. The chosen approach is a Reusable Learning Object (RLO) which consists of an interactive format with audio, text, animations and videos to promote health behaviour change. To this end, this research will co-create a RLO with caregivers to promote responsive feeding.

The aim of this study is to develop a RLO for caregivers of infants under one year to increase awareness, understanding and use of responsive infant feeding behaviours (CRIB). Improving responsive feeding will contribute to the prevention of obesity at an individual and population level. In addition, this study aims to develop infographic guidance for HCPs and support workers to use with caregivers alongside the RLO.

Objectives:To co-design a RLO to increase caregiver awareness, understanding and use of responsive infant feeding behaviours.To create an infographic for HCPs and support workers to improve their knowledge and ability to support caregivers with responsive feeding.To conduct an initial evaluation of the acceptability of the RLO for caregivers and the guidance infographic for HCPs and support workers.To determine the care pathways within the NHS, social care enterprises and the local authority where the RLO will be offered to caregivers with appropriate support.

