##### Analysis

Survey responses will be downloaded to an Excel/Sav file.

Survey 1 responses evaluating RLO content, functionality and usability will be analysed with descriptive statistics in the form of frequencies and percentages. The data will be categorised to highlight areas of function or content that require amending.Survey 2 responses examining the impact and usefulness of the RLO on caregivers will be analysed with frequency tables and descriptive statistics. Data from the closed questions will be analysed to examine the impact of the RLO on changing behaviours related to responsive feeding.Survey 3 responses from HCPs exploring the implementation of the RLO and infographic will be a mixture of quantitative and qualitative data. The quantitative data from the two Likert scale questions will be analysed with frequency tables and descriptive statistics. The qualitative data gathered from the open questions will be analysed using content analysis [34].

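### No Survey 3 item asks about the infographic on its own, so the infographic half of objective 3 has no dedicated measure

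*Protocol article*

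**What the plan says.** The Introduction lists the objectives. The second is "To create an infographic for HCPs and support workers to improve their knowledge and ability to support caregivers with responsive feeding". The third is "To conduct an initial evaluation of the acceptability of the RLO for caregivers and the guidance infographic for HCPs and support workers". It names two products and gives each its own audience.

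Section 2.3.4 (Phase 4) says that both products are evaluated and assigns the work to three surveys. The items of Survey 1 (Table A1) and Survey 2 (Table A2) refer to the RLO or e-learning resource only. Survey 3, answered by HCPs and support workers, "will explore the implementation of the RLO and infographic in practice within the NHS and other organisations". Its make-up is described this way: "Survey 3 will include a mixture of eight open and two closed questions on the implementation of the RLO in practice". The Analysis subsection sends the two rated questions to frequency tables and the open questions to content analysis.

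Table A3 prints the Part 2 items. Two typical ones are "Is the CRIB-RLO/Infographic a good fit with your own values around how you give infant feeding advice" and "Do you understand the information contained in the CRIB-RLO/Infographic".

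**The concern.** The two products differ in kind and in user. The RLO is an interactive resource for caregivers that takes 15 to 20 minutes. The infographic is accompanying guidance for professionals. A health visitor could find one clear and the other confusing. A plain yes to a question that joins them with a slash cannot be assigned to either.

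Survey 3 is the only instrument that mentions the infographic. If its items do not isolate that product, the study may end with little it can attribute to the infographic, and with no sure way of telling which product needs revising before the future trial described in the Discussion. The RLO has two items to itself in the professionals' survey; the infographic, which is made for those professionals, has none.

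**Working it through.** No power or sample-size arithmetic applies. The Design section says: "This study does not involve quantitative hypothesis testing and instead involves an exploratory survey approach where sample size calculations have not been conducted". The check is a count of the ten Part 2 items of Table A3 by the product they name.

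**Step 1: reproduce the plan's own figure.** Items 7 and 9 carry a printed 1-to-5 scale and are closed. Items 1 to 6, 8 and 10 have no response options and are open. That gives 8 open + 2 closed = 10, which agrees with the Method subsection, so the count below covers the whole of Part 2.

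**Step 2: classify each item.**

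| Item | Subject | Type | Product named |
|---|---|---|---|
| 1 | Feelings | Open | Both jointly |
| 2 | Extra effort | Open | Both jointly |
| 3 | Fit with values | Open | Both jointly |
| 4 | Understanding of content | Open | Both jointly |
| 5 | Whether the two work well together | Open | Both, as a pair |
| 6 | Change in team processes | Open | RLO alone |
| 7 | Expected effect on caregivers | Closed | CRIB intervention, undivided |
| 8 | Reason for the score in item 7 | Open | CRIB intervention, undivided |
| 9 | Preparedness to deliver | Closed | CRIB intervention, undivided |
| 10 | Further training needed | Open | RLO alone |

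**Step 3: totals.** Jointly 5, RLO alone 2, undivided 3, infographic alone 0; 5 + 2 + 3 + 0 = 10. Closed items that give a frequency for the infographic alone: 0 of 2.

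**Step 4: compare with the purpose stated in objective 2.** Items on improvement in professionals' knowledge or ability: 0 of 10. Item 4 asks whether the content is understood and item 9 how prepared the respondent is. Both cover the two products together, and neither asks about a change.

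**Step 5: compare the text with the table.** The Method subsection gives the preparedness question with the RLO as its object, whereas item 9 in Table A3 refers to the CRIB intervention. What that rated item covers is therefore itself inconsistent.

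**The case against.** The other side has four good arguments.

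- **The joint items are free text.** Item 1 names both products, and item 3 invites the respondent to describe conflict. Someone who likes the RLO and finds the infographic unclear can write so, and content analysis can code comments by product. This stands. Separate answers are possible, but they rest on at most 30 respondents volunteering the distinction, and items 4 and 5 are phrased so that a bare yes or no is a natural reply.
- **Joint questions suit the design.** The infographic takes images and messages from the RLO and is to be used beside it. Asking about effort or readiness for the package is reasonable in an exploratory implementation survey. This supports keeping item 5 joint. It does not give the infographic's acceptability a measure of its own.
- **Objective 2 is to create the infographic.** A reader might infer that objective 2 goes unanswered. The documents do not support that: producing the infographic meets the wording, and no survey is assigned to measure a gain in professionals' knowledge. Only the stated purpose is untested.
- **Objective 3 is not wholly affected.** A reader might infer that all of it lacks an answer. Surveys 1 and 2 address the RLO half.

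Survey 2 does ask caregivers about gains from the RLO, but its declared aim is impact and that of Survey 3 is implementation, so the contrast carries little weight.

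It cannot be said that the article has merely condensed the form: Table A3 prints the items, and their number matches the text.

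**Conclusion.** The point holds in a limited form. None of the ten Part 2 items isolates the infographic, and no other survey covers it, so the infographic half of objective 3 has no dedicated measure. A separable answer is not ruled out, but it depends on what respondents choose to write. Neither of the two rated items can supply one.

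The documents do not support saying that the study can learn nothing about the infographic.

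The conclusion assumes that Table A3 is the form to be used and that Survey 3 respondents see both products. It is a cheap improvement to an exploratory form, not a flaw that undermines the study.

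**What to change.** 1. Split items 1 to 4 into an RLO line and an infographic line, and keep item 5 as the joint question. The minimum alternative is one instruction above these items asking respondents to comment on the RLO and the infographic separately.
2. State in the Analysis subsection that the open answers will be coded and reported by product.
3. Make the object of item 9 the same in the Method subsection and in Table A3.
4. Optionally, add one or two rated items on whether the infographic improved the respondent's knowledge of responsive feeding and ability to support caregivers. Without a baseline, these give self-perceived gain only and should be reported as such.

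**Cost.** The full split adds four free-text lines and the optional items up to two rated ones, so Part 2 grows from 10 to at most 10 + 4 + 2 = 16 items. The article expects each survey to take no more than 20 minutes and gives no time per item, so a short timing check would be sensible. The single instruction adds no items. Either route needs a form version change, and neither alters the number of participants.
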